#### **6.3.2 Proportional Hazards (PH) Assumption**

Due to our study population being relatively healthy and the lack of significant therapeutic interventions, the potential for treatment-induced time-dependent effects is minimized. However, even in this context, factors such as aging and dynamic changes in protein expression over time could still lead to violations of the PH assumption. To validate this assumption, we will use Schoenfeld residuals tests to assess the correlation between residuals and time. Graphical diagnostics, such as log-minus-log survival plots, will also be employed to verify that the hazard functions remain parallel across groups. If any covariate exhibits evidence of non-proportionality, we plan to introduce time-dependent covariates or apply stratified Cox models to adequately adjust for such effects.

### **6.4 Feature Selection and modeling**

#### **6.4.1 Training and Testing Set**

The datasets will be partitioned into a training set comprising 80% of APOL1-HR PMBB participants and a testing set comprising 20%. To maintain balance between the training and validation sets, we stratify based on key clinical parameters, which will be detailed in the Table of the main text.

### **6.4.2 Regularized Cox Regression:**

We will perform a regularized Cox Regression where the L1/L2 ratio varies from 0 to 1. An alpha grid is automatically generated by sklearn and sksurv using 8-fold cross-validation, and the optimal alpha is selected based on the minimization of the partial likelihood deviance. Specifically, for a given L1 ratio, the model will be fitted using CoxnetSurvivalAnalysis (with an alpha\_min\_ratio set to 0.00001 and a maximum iteration of 1000), and a subset of alpha values is extracted for tuning. At each iteration we randomly sampled (with replacement) protein subsets drawn from the top 20% of proteins ranked by univariate AUC and fit the model on those subsets. This procedure was repeated across approximately 1 million different protein combinations.

### **6.4.3 Final modeling:**

After the iterative sampling and model fitting process, the best-performing model was identified based on the lowest cross-validated partial likelihood deviance within the testing set. The final set of selected proteins and their corresponding coefficients were then used to construct the prognostic model. This finalized model was refitted on the entire training dataset to derive the final coefficients, which were subsequently applied to generate the APOL1 Proteomic Risk Score (APRS) with the clinical confounders for downstream validation and external cohort analyses.

### **6.5 Number needed to treat (NNT)**

For a chosen horizon (e.g., 5 or 10 years), each subject will be classified as having an event by that time or not. For each score and threshold (evaluated across score percentiles), the observed event rate among subjects at or above the threshold is calculated, then multiplied by an assumed treatment relative risk reduction (RRR) to obtain the absolute risk reduction; the reciprocal of this value yields the NNT. Confidence intervals for NNT will be obtained by nonparametric bootstrap (1,000 resamples). Reported NNTs are presented across thresholds (NNT curves) and at selected operating points (e.g., the 95th percentile in the revision); thresholds that select no subjects or yield no positive risk reduction are not reported. NNTs are shown under a range of plausible RRRs (e.g., 15–60%), and a trial-informed example is also reported when an RRR is available.

```

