### **3.6 Study Endpoints and Follow-Up**

The primary endpoint is a composite defined as the earliest of: (1)  $\geq 40\%$  decline in eGFR from baseline; (2) onset of kidney failure (initiation of maintenance dialysis or kidney transplantation); or (3) all-cause mortality. These criteria mirror standard endpoints in CKD trials. Follow-up begins at the date of the index blood draw and continues until occurrence of the composite event, death, loss to follow-up, or end of study (up to ~10 years). Participants will be censored at the time of death if it precedes kidney endpoints, loss to follow-up, or at 10 years of follow-up to ensure comparability across cohorts.

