### **3.7 Statistical Analysis**

The APOL1–high-risk cohort will be randomly divided into an 80% training set and 20% test set (stratified by outcome incidence). In the training set, candidate proteins will be selected via an elastic-net penalized Cox proportional hazards regression (age, sex, baseline eGFR, and log2(UACR) included as unpenalized covariates). Tuning parameters ( $\alpha$ ,  $\lambda$ ) will be chosen by 8-fold cross-validation. The final APRS model will include the nine selected proteins plus the four clinical covariates. Model discrimination will be quantified

by time-dependent AUC (tAUC) at prespecified time points and Harrell's C-index. Model performance will be compared to the KFRE (4-variable equation) and established CKD risk scores.

Proportional hazards assumptions for APRS and covariates will be tested using Schoenfeld residuals. Sensitivity analyses will address potential biases: we will apply inverse-probability-of-censoring weighting (IPCW) to account for informative loss-to-follow-up, computing weights within the training set. Feature stability will be assessed via bootstrap resampling. We will compute net benefit using decision-curve analysis (assuming equal weight for false positives and negatives). To gauge clinical utility, we will calculate the number needed to treat (NNT) to prevent one composite event under a hypothetical APOL1-targeted therapy: assuming a relative risk reduction of 27% (as reported for inaxaplin), NNT will be derived as the reciprocal of the absolute risk reduction. Comparisons of NNT between APRS-based risk stratification and standard models (KFRE) will be reported. All tests will be two-sided with  $\alpha=0.05$ .

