## **3 Cohorts, inclusion criteria, and analytic sets**

Primary derivation set (APOL1-HR, preserved eGFR):

Inclusion: APOL1 genotype = high-risk (two risk alleles: G1/G1, G2/G2, G1/G2), available plasma proteomics (SomaScan platform), baseline eGFR > 60 mL/min/1.73 m^2 measured at or 2 months before or 1 month after of sampling, available UACR (or imputed as specified).

Final sample size in derivation set:  $N = 851$ . Baseline descriptive statistics, event counts, and follow-up summaries are provided in manuscript. Key cohort summary (derivation APOL1-HR preserved-eGFR): mean age 49.2 years; female proportion 66.5%; mean eGFR 90.6 mL/min/1.73 m^2; median UACR 17.23 mg/g; composite event rate 17.98% ( $n = 153$ ); mean time to event 6.51 years; median follow-up 7.3 years.

Secondary analytic sets:

APOL1-HR with existing CKD at baseline: 262 participants included for comparison and benchmarking of APRS behavior in established disease.

APOL1-low-risk extension: an additional 995 participants to evaluate specificity and cross-genotype performance.

EUR comparison set (review-only):  $N = 514$  (used for method comparisons but not central to the APOL1-focused primary aims).

External validation cohorts

ARIC (Atherosclerosis Risk in Communities): African-ancestry subset with SomaScan proteomics (where available).

UK Biobank (UKB): African-ancestry subset with Olink proteomics (smaller targeted panels). Because platforms differ, apply the prespecified cross-platform mapping and multi-output imputation.

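### The NNT in SAP 6.5 uses a crude event proportion that makes no allowance for participants censored before the horizon; at 10 years this overstates NNT by roughly a quarter to a half for the cohort as a whole

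*Combined protocol and SAP*

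**What the plan says.** SAP 6.5 sets the time frame loosely: "For a chosen horizon (e.g., 5 or 10 years" are its examples. At the chosen horizon "each subject will be classified as having an event by that time or not". For each score and threshold, "the observed event rate among subjects at or above the threshold is calculated". That rate is multiplied by an assumed relative risk reduction (RRR), and the reciprocal is the NNT. Intervals come from a bootstrap with 1,000 resamples. On the RRR, Protocol 3.7 has "assuming a relative risk reduction of 27% (as reported for inaxaplin"; SAP 6.5 adds "NNTs are shown under a range of plausible RRRs (e.g., 15–60" percent.

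Neither section says how a participant whose follow-up ends event-free before the horizon is handled. Inverse-probability-of-censoring weighting (IPCW) appears in SAP 7, for the performance metrics, and in Protocol 3.7, as a sensitivity analysis. Neither place links it to NNT.

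Protocol 3.7 also contains the only specification of net benefit: "We will compute net benefit using decision-curve analysis (assuming equal weight for false positives and negatives". The SAP has no decision-curve section, no threshold range and no censoring rule for net benefit.

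**The concern.** A participant censored event-free at year 4 has unknown status at year 10. A yes-or-no classification of every subject has nowhere to put that person except among the non-events. The person stays in the denominator although a later event could never be counted, so the estimated risk is too low and the NNT too high. The bootstrap does not help, because each resample repeats the same estimator and the interval is centred on the biased value.

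The affected group is large at 10 years. SAP 3 gives "mean time to event 6.51 years; median follow-up 7.3 years", and Protocol 3.6 censors administratively "or at 10 years of follow-up to ensure comparability across cohorts". What is at stake is the absolute NNT reported to convey clinical utility, and to a lesser and unknown extent the planned NNT comparison between APRS and KFRE.

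The decision-curve clause raises a separate, smaller question. Net benefit weights a false positive by the odds of the threshold probability, so fixing that weight at one fixes the threshold.

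**Working it through.** **Inputs**

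- Derivation cohort 851, composite events 153 (17.98%), mean time to event 6.51 y, median follow-up 7.3 y: SAP 3.
- Follow-up mean 7.18 y, SD 2.89 y: Appendix 1 of the protocol.
- Follow-up capped at 10 y: Protocol 3.6.
- RRR 27%: Protocol 3.7. RRR 15% to 60%: SAP 6.5.

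**1. Reproduce the stated rate.** 153/851 = 17.98%. Training plus test from Supplementary Table 1 gives (121 + 32)/(680 + 171), the same. The documents state no NNT.

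**2. How many are unobserved at 10 years?** With median follow-up 7.3 y, about 425 of 851 have 7.3 y or less. Even if all 153 events fell among them, at least 425 − 153 = 272 (32% of the cohort) are event-free with unknown 10-year status. Under the censoring patterns assumed in step 5 the share is about 59% to 77%.

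**3. Crude NNT as specified.** NNT = 1/(RRR × risk) = 1/(0.27 × 0.1798) = 20.6.

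**4. Allowing for censoring, constant hazard.**

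- Person-time: 851 × 6.51 = 5,540 y
- Rate: 153/5,540 = 0.0276 per year
- 10-year risk: 1 − exp(−0.276) = 24.1%
- NNT: 1/(0.27 × 0.241) = about 15.3

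The crude NNT is therefore about 34% too high.

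| RRR | Crude NNT | Allowing for censoring |
|---|---|---|
| 15% | 37.1 | 27.6 |
| 27% | 20.6 | 15.3 |
| 60% | 9.3 | 6.9 |

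This treats 6.51 y as the mean over all subjects. Appendix 2 supports that: the matched low-risk group has only 3 events among 38, yet its mean time to event is 7.25 y, close to its mean follow-up of 7.42 y. Using the longer 7.18 y as person-time instead gives 153/(851 × 7.18) = 0.0250 per year, 10-year risk 22.2% and NNT 16.7.

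**5. Sensitivity.** Weibull event times (shape 0.7, 1.0, 1.5) were combined with two assumed censoring distributions: a beta scaled to 10 y and a normal capped at 10 y. Both were matched to mean 7.18 and SD 2.89, and the event scale was set to reproduce 17.98% observed.

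- 10 years: risk 22.7% to 26.9%, NNT 13.8 to 16.4. Crude NNT 26% to 49% too high.
- 5 years: crude NNT about 9% to 15% too high (constant hazard: 31 to 32 against about 28).

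The medians of the assumed censoring distributions (7.9 and 8.3 y) exceed the stated 7.3 y, so these ranges are indicative.

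**6. The other crude reading.** Dropping participants of unknown status removes event-free people and keeps events. In the same models the 10-year event rate becomes 44% to 80% and the NNT about 5 to 8.

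**7. Decision curve.** Net benefit = TP/n − (FP/n) × pt/(1 − pt). Equal weight means pt/(1 − pt) = 1, so pt = 0.50. The treat-all reference shows how far this lies from the cohort's average risk:

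| pt | Treat-all, risk 18.0% | Treat-all, risk 24.1% |
|---|---|---|
| 0.10 | +0.09 | +0.16 |
| 0.20 | −0.03 | +0.05 |
| 0.50 | −0.64 | −0.52 |

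**The case against.** **The text does not say that censored people are event-free.** True. That is the plain reading of a yes-or-no classification of every subject, but dropping them is possible, and it biases NNT the other way. Neither reading gives a valid 10-year risk, so the objection changes the certainty about direction and leaves the need for a rule.

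**Most of the bias cancels between scores.** A reader might infer that the APRS-versus-KFRE comparison is materially distorted. The documents do not support that. As an illustration, take one assumed follow-up pattern (34% reach 10 y, the rest uniform from 1.5 to 10 y; its median of 7.9 y again exceeds 7.3 y) with constant hazards. The 10-year NNT is inflated 1.37-fold at 15% true risk, 1.31-fold at 50% and 1.23-fold at 80%. The ratio of two NNTs is then distorted by about 7% (50% against 80% groups: 1.31/1.23) or 11% (15% against 80%: 1.37/1.23), and by about 2% or less at 5 years. If follow-up differs between the groups that the scores select, the distortion could be larger or smaller, but no figure is given for those groups. The objection largely stands.

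**NNT is illustrative.** It appears in none of the protocol's objectives nor in the SAP's primary aim, the therapy is hypothetical, and the RRR range alone moves NNT four-fold. This stands as an argument on severity. Varying the RRR does not correct the risk, however, because the same bias runs through every RRR.

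**Net benefit at 0.50 is a valid number.** Agreed. A reader might call the decision-curve result wrong, but the documents do not support that either. The 0.50 is inferred from the equal weights and is not stated, and a score that picks out a small high-risk group might reach such risks. What stands is that one fixed weight contradicts the idea of a curve and says nothing about lower thresholds.

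**Conclusion.** The concern holds for NNT, mainly at 10 years. SAP 6.5 has no allowance for censoring before the horizon. On the plain reading the whole-cohort 10-year risk is 18.0% instead of about 24% (22.7% to 26.9%), and NNT at 27% RRR is 20.6 instead of about 15 (13.8 to 16.4). At 5 years the effect is modest.

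These figures assume non-informative censoring, 6.51 y as all-subject observed time, and the hazard shapes and censoring patterns listed. They describe the whole cohort. The documents give neither event rates nor follow-up above any score threshold, so the bias at an operating point such as the 95th percentile cannot be computed. Score derivation, discrimination and external validation are untouched.

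The equal-weight clause in Protocol 3.7 is an internal inconsistency: it reduces the curve to one inferred threshold, uninformative about lower ones. Severity for both: should be fixed.

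**What to change.** **SAP 6.5.** Replace the observed event rate with 1 minus the Kaplan-Meier estimate at the horizon among participants at or above the threshold, or with an IPCW estimate. Recompute it within each bootstrap resample. Kaplan-Meier suits this endpoint because SAP 6.3.1 counts death as an event; the sentence in Protocol 3.6 that censors at death should be reconciled with that. Report the number still at risk at the horizon: the top 5% is about 43 of 851, or about 9 of the 171 in the test set, so 10-year estimates there will be imprecise.

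**Protocol 3.7.** Delete the equal-weight clause. Prespecify a range of threshold probabilities chosen by the investigators, weight false positives by pt/(1 − pt), use censoring-adjusted counts of true and false positives, and show treat-all and treat-none as references.

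**Cost.** A few sentences and a small code change, with no new data. Reported 10-year NNTs will change. Intervals may widen, because they will reflect the information actually available at 10 years.

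### SAP 6.5 leaves out NNT thresholds with no positive risk reduction; under a fixed positive RRR this can only mean zero events, so only a score's worst results go unreported

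*Combined protocol and SAP*

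**What the plan says.** SAP 6.5 (Number needed to treat) starts from a binary outcome at a chosen horizon: "each subject will be classified as having an event by that time or not". The event rate among people at or above a score threshold is "then multiplied by an assumed treatment relative risk reduction (RRR) to obtain the absolute risk reduction", and NNT is the reciprocal. Every RRR named is positive. SAP 6.5 says "NNTs are shown under a range of plausible RRRs (e.g., 15–60" per cent), and Protocol 3.7 works its example "assuming a relative risk reduction of 27% (as reported for inaxaplin").

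Results are presented as curves over score percentiles and "at selected operating points (e.g., the 95th percentile in the revision"), with confidence intervals from 1,000 bootstrap resamples. SAP 6.5 then adds that "thresholds that select no subjects or yield no positive risk reduction are not reported". Protocol 3.7 makes the comparison a deliverable: "Comparisons of NNT between APRS-based risk stratification and standard models (KFRE) will be reported".

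Section 6.5 does not say in which set the NNT is computed. It asks for no count of omitted thresholds, gives no rule for resamples without events, and names no treat-all reference.

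**The concern.** The exclusion reads like a safeguard against showing an NNT where treatment does no good. It cannot do that job, because benefit is assumed through the RRR and not estimated. The only quantity that varies is the event rate among those selected, and ARR fails to be positive only when that rate is zero. The thresholds left out are those where everyone the score ranked highest stayed event-free.

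The filter also acts on each score separately. The APRS and KFRE curves may therefore cover different percentiles, and a gap would not show whether the score selected nobody or selected only people without events. This matters most at the 95th percentile and above, where a small cohort leaves few people. The bootstrap raises a related question: a resample with no events has an infinite NNT, and the plan does not say how it enters the interval.

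**Working it through.** **Inputs.** Test set: 171 people, 32 composite events (Supplementary Table 1). Full derivation set: 851 people, 153 events (SAP 3). ARIC high-risk: 314 (Protocol 3.3). UK Biobank high-risk: 204 (Protocol 3.4). RRR: 27% (Protocol 3.7). Five-year, ARIC and UK Biobank event rates are not in the documents, so ranges are assumed.

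**Stated figures reproduced.** 32/171 = 18.71%, as in Supplementary Table 1. 153/851 = 17.98%, as in SAP 3 ("composite event rate 17.98" per cent). The documents state no NNT.

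**Step 1: what the condition means.** ARR = rate × RRR. With RRR between 0.15 and 0.60, ARR ≤ 0 requires rate = 0.

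**Step 2: treat-all reference.** NNT = 1/(rate × 0.27).
- Test set: 1/(0.1871 × 0.27) = 19.8
- Full set: 1/(0.1798 × 0.27) = 20.6

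**Step 3: how often the rule fires for an uninformative score.** If the score carries no information, the events among the n top-ranked people are hypergeometric, so P(omitted) = C(N − D, n)/C(N, n), with N people and D events.

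| Set and percentile | n | Events assumed | P(omitted) |
|---|---|---|---|
| Test set, 90th | 18 | 32/171 | 1.9% |
| Test set, 95th | 9 | 32/171 | 14.7% |
| Test set, 97.5th | 5 | 32/171 | 35.0% |
| Test set, 99th | 2 | 32/171 | 66.0% |
| Test set, 95th, rate about 15% (assumed) | 9 | 26/171 | 21.8% |
| Test set, 95th, rate about 10% (assumed) | 9 | 17/171 | 38.0% |
| Test set, 95th, rate about 5% (assumed) | 9 | 9/171 | 60.7% |
| Full set, 95th | 43 | 153/851 | 0.02% |

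For UK Biobank (11 people) and ARIC (16 people) at the 95th percentile, assumed rates of 5–19% give 3–57%.

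**Step 4: effect on what is reported (test set, 95th percentile, RRR 27%).** With k events among 9, NNT = 9/(0.27k).
- k = 0, probability 0.147: NNT infinite, omitted under the rule
- k = 1, probability 0.324: NNT 33.3, worse than treat-all (19.8)
- k ≥ 2, probability 0.529: NNT 16.7 or lower, better than treat-all

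The share better than treat-all is 52.9% of all draws and 0.529/0.853 = 62.0% of reported ones. The mean reported event rate rises from 18.7% to 0.1871/0.853 = 22.0% (21.95% before rounding). In the full set the share is 52.2% with or without the rule.

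At the assumed 10% rate, one event in 9 is 11.1%, already above the cohort rate of 17/171 = 9.9%. Every NNT that survives the rule then beats treat-all, against 62.0% of all draws.

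**Step 5: bootstrap.** If k of the 9 selected people have events and those 9 are resampled, the share of resamples with none is ((9 − k)/9)^9.
- k = 1: 34.6%
- k = 2: 10.4%
- k = 3: 2.6%

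Each exceeds 2.5% (k = 3 only just), so the 97.5th percentile of the bootstrap NNT is infinite. Dropping those resamples would give a finite limit.

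**The case against.** A reader might infer that, because of this rule, an uninformative score yields a favourable NNT most of the time. The documents do not support that. At the test set's own rate a finite NNT is common (85.3%), but one better than treat-all occurs in 52.9% of draws. That is close to a coin toss and is there without the rule, which adds about 9 points among reported results. In the full 851 it adds nothing.

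Nor is every summary of the reported NNTs biased low. Inverting the 22.0% mean reported rate gives about 17, but the mean of the reported NNTs themselves in Step 4 is (0.324 × 33.3 + 0.304 × 16.7 + 0.160 × 11.1 + 0.052 × 8.3 + about 0.1 for k ≥ 5)/0.853 ≈ 21.3. That is slightly above the treat-all 19.8.

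Other points on this side are fair. Zero events among 9 people is the worst possible result, yet it is weak evidence against a score, since chance alone produces it 15% of the time. NNT is undefined there, the rule is disclosed in advance, and a blank at a named operating point would be noticed. NNT is a hypothetical illustration and is not among the Protocol 2 objectives; discrimination and decision-curve net benefit are assessed separately. The omission rule is written for thresholds, so it cannot be read as a plan to drop resamples. That is a gap in specification only.

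These points limit the size of the problem. They do not change what the rule removes or the direction in which it works.

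**Conclusion.** The point holds as a defect in a reporting rule. Given a fixed positive RRR, the exclusion is equivalent to having no events, so it screens out only the least favourable results and does so score by score.

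Its effect ranges from negligible (0.02% of draws in the full 851 at the 95th percentile) to moderate (14.7% in the test set, about 38% if the horizon rate is assumed to be 10%). It grows at higher percentiles. Since 6.5 names no analysis set, the plan does not settle which of these applies. In small sets the missing bootstrap rule also matters: with one to three events among nine people, a finite upper NNT limit could come only from dropping the zero-event resamples.

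The figures assume an uninformative score, overall event proportions standing in for the horizon rate, no adjustment for censoring (6.5 states none), and, for Step 5, resampling of the selected people. The algebra in Step 1 needs only a positive RRR.

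**What to change.** In SAP 6.5:
- Delete the exclusion for thresholds without positive risk reduction. Keep the one for thresholds that select nobody, where nothing can be estimated.
- Report the same prespecified percentiles for APRS and KFRE, with the number selected and the number of events at each.
- Show a zero-event threshold as ARR = 0, NNT not estimable (infinite).
- Compute bootstrap intervals on the ARR scale and invert them, with an upper NNT limit of infinity where the ARR interval reaches 0.
- Add the treat-all NNT as a reference line (about 20 at RRR 27%).
- Name the analysis set for each NNT curve.

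A minimum number selected, such as 20, is not advised. It would remove the named 95th-percentile point in the test set (9 people), UK Biobank (10 or 11) and ARIC (16). Showing n and events gives the reader the same warning.

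The cost is a few sentences in the SAP and a small code change. The downside is that some NNT intervals become open-ended.
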